## Abstract

**Introduction:**

Early childhood experiences have a lifelong impact on a child’s future. Social and environmental experiences and interactions have a profound relational effect on children’s physical and mental health which transfers agency to parents, caregivers and duty-bearers to care for the child’s welfare. In the Australian context early child development indices have been in decline in some communities. Hence, there is a sense of urgency to reverse these trends from an integrated perspective. A multisector, multi component program of interventions named *A Good Start in Life* is proposed and is being tested in the Australian Capital Territory across suburbs with high levels of early childhood development disadvantage. The aim of this study is to evaluate the outcomes and processes related to targeted interventions, designed to integrate child and family services within the local district and embed allied health programs into early childhood education, care services and playgroups.

**Methods and analysis:**

The *Good Start in Life* study will use a quasi-experimental design (with a matched control geographical area) consisting of a combination of interventions that will build multisectoral collaboration across education, health and social services that connect and support families with children from birth to 5 years. The control area will be matched on demographic characteristics and early child development outcomes and trends over the pre-intervention period. Evaluation data will be collected at baseline, and then on an annual basis for a further three years. A mixed methods approach will be used to evaluate delivery processes: quantitative (checklists, questionnaires) and qualitative methods (observations, focus groups and key stakeholder interviews). Effectiveness of the programme will be evaluated by comparing early child development outcomes between the comparator areas from the Australian Early Development Census in 2024. The primary focus will be on reducing the number of children who are developmentally vulnerable on at least one early development index (EDI). Separate tests will be conducted for significant differences in the percentage of children at risk in each of the five individual EDI domains. These domains are physical health and wellbeing, social competence, emotional maturity, language and cognitive skills, and communication and general knowledge.

**Trial registration:**

ACTRN12621001140842.

## Introduction

Early childhood experiences and interactions have a profound influence on a child’s physical, cognitive, social and emotional development [1, 2] and form the critical foundation for their lives [3–5]. The social circumstances into which children are born determines their exposure to events that are either beneficial or detrimental to their development [6]. How well children grow and thrive depends on the nurturing conditions of their environment in the widest sense, and this is fundamentally important in the early years (under 5 years) when the brain and body are developing rapidly [7]. The primary provider of beneficial early development opportunities are the child’s parents and caregivers. However, most parents cannot provide strong supportive environments without the assistance of formal and informal support services When parental support is compromised, for example due to factors such as sustained poverty, family break-up, family violence, abuse, neglect, illness or disability, then some of the child’s beneficial development opportunities must be provided by external support mechanisms. Unfortunately, contemporary trends indicate that the prevalence of such adverse circumstances in Australia have been worsening [8].

In response to this issue, the Australian government established the Australian Early Development Census (AEDC) in 2009, to provide a national measurement programme to monitor Australian children’s development. The AEDC is undertaken every three years. There have been four waves of measurement, the last one being completed in 2018. The census involves teachers of children in their first year of full-time school (age 5–6 years) completing the Australian version of the Early Development Instrument [9]. The Instrument consists of approximately 100 behavioural and competency-based questions and collects data relating to five key areas of early childhood development, referred to as ‘domains’. These include: physical health and well-being; social competence; emotional maturity; language and cognitive skills (school based); communication skills and general knowledge.

Over the last three censuses (2012–2018), the Australian Capital Territory (ACT) has seen an increase in the proportion of children who are developmentally vulnerable on all but one of the AEDC domains and the two summary domains, vulnerable on one or more domains and vulnerable on two or more domains [10]. As a result, early childhood development has been a focus recently in the ACT. Early investigations have shown that services, organisations, and sectors continue to operate in isolation, and, as a result, it has been reported that families struggle to access cohesive and holistic pathways of care for their children. Examining the variation in early childhood vulnerability across suburbs making up the ACT’s nine districts reveals greater developmental vulnerability is experienced in clusters of suburbs. According to the 2018 AEDC, 26.4% of 5-year-old children in the Belconnen district were developmentally vulnerable in one or more domains [11].

An inventory of all early childhood services in the Belconnen district in 2019 revealed that there were multiple services across the education, health, and social services sectors in operation. These included but were not limited to Early Childhood Education and Care (ECEC) services, playgroups, preschools and parenting programs. However, evidence suggests that vulnerable families are unable to or choose not to access these services, or are not aware of them [12]. The fragmented nature of service delivery and accessibility, particularly across centres and services, hinders referrals and restricts pathways of care for children with developmental needs. Under these conditions developmental issues are not addressed, while the number of children entering school with significant social, communication, behaviour and health challenges continues to increase. Research confirmed that when such challenges are present on entering formal education, there are cascading effects throughout the school years and later in life [3, 4]. These children are more likely to experience poor academic achievement, early drop-out from school and unemployment [13].

Literature on integration between early childhood centres reports that improving collaboration between services by creating more connected and productive early childhood programmes and networks provides better opportunities for positive outcomes for children and families [14]. Further studies have shown that the creation of a “virtual” network in which services do not need to relocate to a singular location produces the same benefits as co-located services [15].

As the nature of service integration prohibits a singular definition, a fit-for-purpose, context-and cultural- specific definition needs to be developed. In this project, the development of a definition will be considered as an outcome as this is an iterative process and will be refined throughout the project to represent the context, nature, and function of the integrated network most accurately. Broadly, this project views service integration as the creation of or strengthening of agency between early childhood services and programs across sectors within the local area. Such integration should provide a more comprehensive connection for families and greater numbers and quality of developmental opportunities for children, leading to better outcomes.

This project aims to evaluate an intervention designed to integrate child and family services within the district and embed allied health programs into early childhood education and care services and playgroups and to evaluate the outcomes and processes of the intervention. The Project Management Team (PMT) collaborate with local services to form a network of related services for children aged between birth and 5 years across the health, education, and social services sectors, allowing families to more easily access and navigate through different services.

The two main aims for this project are:

To create an integrated network of services for young children and families in target suburbs in the Belconnen district in the ACT.To reduce the proportion of developmentally vulnerable children in the target suburbs of the Belconnen district in the ACT.

The following questions will be addressed:

Does a multi-sector, multi-component approach reduce the proportion of children who are considered developmentally at risk in the intervention community compared to the control community?What is the reach, participation, intervention quality and dose of the interventions delivered and what were the barriers to, and facilitators of, implementation?

## Methods and analysis

### Design and intervention

This study will use a quasi-experimental design to determine the effectiveness of creating an integrated service network on reducing developmental vulnerability in young children. The formative components of the project commenced in November 2020 and the project will conclude in March 2024. The intervention will take place in the Belconnen district, chiefly within services located in the nine identified target intervention suburbs, while the Tuggeranong district will serve as the ‘control’ site. These two districts are well-matched on socio-demographic characteristics and on early child development outcomes from the most recent three censuses. Data will be collected from the AEDC for comparison, but no intervention will occur within this district other than those that are to be expected in a large urban area. The intervention will be conducted using a ‘staggered’ approach, starting with four suburbs (in two clusters) in the first year and ending with all nine suburbs (four clusters) receiving the intervention by the fourth year. An integrated multi-sector programme will be delivered to children and families in multiple settings in the intervention suburbs through a wide range of programmes and services that focus on the 5 AEDC domains of childhood development: physical health and wellbeing, social competence, emotional maturity, language and cognitive skills, and communication and general knowledge. The list of programs to be implemented are presented in Appendix 1 in S1 File. To help achieve key aims of this project, a family liaison coordinator will be employed. The role of this coordinator will be to work within the community to connect families to services and to facilitate the creation of referrals for children with additional needs. In addition, the family liaison coordinator will work with services to better connect them to other related services and to the wider community.

To achieve the second aim of this project, allied health programs will be embedded and delivered ‘in place’ into early childhood services within the intervention suburbs. Through a partnership with the University of Canberra, students from speech pathology, occupational therapy, health, nutrition, and education disciplines will work with a clinical educator to implement programs into early childhood services as a part of their work integrated learning. The programs will either function as professional learning for ECEC educators and playgroup facilitators or provide on-site clinical advice and support.

To supplement the aims and objectives of this project, other existing services and activities will be delivered to target suburbs within the community. Formal partnerships, marked by the creation of memoranda of understanding between organisations and the project, will be developed to ensure a clear understanding of the aims and scope of the partnership as well as to facilitate the creation or modification of services and programs to better address the needs of children and their families. This may include creating new programs, providing resources or funding to facilitate existing programs within intervention suburbs, or expanding current programs to reach more children and families. Within intervention suburbs, ‘loose parts play’ and ‘nature play’ as enabling environments will be held in suitable local settings e.g. parks, community halls, public spaces [16]. These place-based activities will be open to the public in non-stigmatising ways to engage local parents and caregivers who may not have been previously involved with other services due to lack of accessibility.

### Participants

The nine suburbs were selected using AEDC data from three censuses: 2012, 2015 and 2018. Suburbs were considered for the intervention if they had shown a worsening trend in vulnerability in at least three EDI domains and the ‘vulnerable in one or more domains’ category. These suburbs were then grouped into four ‘clusters’ based on geographical location, as shown in Appendix 2 in S1 File. This was done in order to target communities where we hypothesize that better integrated services will maximise the reach and number of quality early development opportunities for children.

The services invited to participate in the project were selected if they met the following criteria. First, the service must be located within one of the nine intervention suburbs or belong to one of the partner organisations and be located within the Belconnen district. Second, the service must target children aged birth to five years. The service must also pass a risk assessment and have educators who are willing and able to complete the programs and consent to data collection and a recorded follow-up interview.

ECEC educators, directors, and parents must be able to provide written consent before participating in any programs. Parents must also provide consent for their children if they are involved in any programs. Children will be asked to verbally consent to being involved in any activity outside of their regular ECEC schedule. An information sheet detailing the program and the role and expectations of the educator will be provided to them prior to commencing and must be signed and dated by both the educator and the PMT before being accepted into the project. The information sheet will also stipulate that participants are free to withdraw at any time and that all data pertaining to the participant, including interview recordings, will be removed from the study if requested.

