#### Developmental vulnerability

The primary aim, to reduce the proportion of children who are developmentally vulnerable, will be measured by comparing results from the AEDC. A baseline measurement was recorded using the 2018 AEDC data for each intervention suburb. The comparative data will be taken from the 2024 AEDC results. The two timepoints will be analysed to see if there has been a significant decrease in the proportion of children in the ‘developmentally vulnerable in one or more domains’ category, as well as across all five EDI domains. The 2021 census data will not be used in this study due to disruptions to service delivery in 2020. Additionally, the interventions will have been running for less than a year at the time of the data collection, and therefore not enough dose will have been given to result in any significant impact on AEDC scores.

*Outcome measures*. Every three years the Early Development Instrument of the AEDC measures the five domains of early development described above in Australian children who are commencing their first year of full-time school. Under each of these domains, children are classified into one of three categories: developmentally on track, developmentally at risk and developmentally vulnerable. Summary indicators are then calculated for each community based on the proportions of children in each of these three categories. The primary focus for this study will be to reduce the proportion of children in the intervention community who are classified as developmentally vulnerable on one or more domains. We will also perform separate tests for significant change in the percentage of children at risk in each of the five individual EDIs.

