*Sample size estimates*. Our sample size calculation is based on the AEDC ‘critical difference estimates for communities’ [17]. We will focus the intervention on those suburbs (SA2) in the two poorest performing districts with the highest proportions of children with at least one EDI domain in the developmentally vulnerable category at the most recent census. For example, based on 2018 census results, ~40% of this sample have been classified as developmentally ‘at risk’, i.e. falling significantly behind their peers, and could benefit from early intervention. We anticipate that approximately half of this number, ~250–300 children, will be required to show a statistically significant difference. Our primary focus will be on reducing the number of children who are developmentally vulnerable on at least one index (Table 1). We will also perform separate tests for change in the percentage of children at risk in each of the five EDIs.

**Table 1 pone.0267666.t001:** Critical differences (%) to establish significant change for each of the six early development indices.

Community size (# of children)	Developmentally vulnerable (1+) (%)	Physical Health & wellbeing (%)	Social competence (%)	Emotional maturity (%)	Language & cognitive skills (%)	Communication & general knowledge (%)
200–299	4.7	5	4.6	4.9	4.8	5.2

Time-point comparisons will be made between 2021 and 2024 AEDC indices for both intervention and comparator areas. Across-area comparisons will be made between intervention and comparator areas for the 2024 census indices.

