#### Quantitative analysis

Testing for statistically significant differences in children’s early development indices will be based on the critical difference approach developed for the AEDC by Gregory and Brinkman [17]. The Gregory and Brinkman report provides the technical details to determine “how big” a difference (%) needs to be in the EDI results between two different time points or two different areas to be considered statistically significant [11, Tables 14 –primary outcome and 13 –the five secondary outcomes, respectively]. The method allows for the expected sample to sample variation and typical measurement error associated with the sort of data collected in the AEDC. Current versions of the methodology allow us to compare two point-estimates, either across time or between neighbourhoods, of the selected index. Table 1 shows the critical differences that will be needed to establish a significant change for each of the six EDI indices,—the primary outcome and five secondary outcomes—to be considered in this study. The population of children in the intervention and control areas is expected to be in the range 200–299 at the 2024 census. Time-point comparisons will be made between 2021 and 2024 AEDC indices for both intervention and comparator areas. Across-area comparisons will be made between intervention and comparator areas for the 2024 census indices. The following hypotheses will be tested for each of the six indices to be used in this study:

Each EDI for the intervention suburbs (within the Belconnen district) for the 2024 census will be significantly lower, i.e. show a significant reduction in the proportion of children who are developmentally vulnerable or at risk, compared to that in the control suburbs (within the Tuggeranong district)Each EDI for the intervention suburbs (within the Belconnen district) for the 2024 census will be significantly lower, i.e. show a significant reduction in the proportion of children who are developmentally vulnerable or at risk, compared to the corresponding value in the 2021 census

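### If 2018 is the baseline, suburbs selected for worsening up to 2018 can appear to improve by the 4.7-point threshold through regression to the mean alone; the article also contradicts itself on the baseline, and the district-level match does not cure this

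*Protocol article*

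**What the plan says.** All references are to the Protocol article.

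- **Selection (Participants).** "The nine suburbs were selected using AEDC data from three censuses: 2012, 2015 and 2018". The rule is: "Suburbs were considered for the intervention if they had shown a worsening trend in vulnerability in at least three EDI domains", together with worsening in the one-or-more-domains category. That category is the primary outcome.
- **Selection (Sample size estimates, under Developmental vulnerability).** A different rule: "We will focus the intervention on those suburbs (SA2) in the two poorest performing districts with the highest proportions of children" vulnerable on at least one domain at the latest census. This is a rule on level, not trend, and it names two districts. Participants and Design and intervention describe nine suburbs in Belconnen alone.
- **Baseline (Developmental vulnerability).** "A baseline measurement was recorded using the 2018 AEDC data for each intervention suburb". The comparison year is 2024, and "The 2021 census data will not be used in this study due to disruptions to service delivery in 2020".
- **Baseline (Sample size estimates; Quantitative analysis).** The time comparison is 2021 against 2024 in both areas, and the second hypothesis uses 2021.
- **Comparator.** Design and intervention says: "These two districts are well-matched on socio-demographic characteristics and on early child development outcomes from the most recent three censuses". The Abstract says the control area will be matched on outcomes and pre-intervention trends. The first hypothesis has the 2024 intervention value "compared to that in the control suburbs (within the Tuggeranong district").
- **Tests.** The change over time and the 2024 difference between areas are each held against a critical difference. For the primary outcome this is 4.7 points at a community size of 200-299 (Table 1).
- **Limitations (Discussion).** Regression to the mean is not mentioned.

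**The concern.** The last point of the selection trend is also the before-value of the evaluation. A suburb qualifies more easily when its 2018 figure happens to be high by chance, and that chance element does not recur in 2024. The 2018-to-2024 change therefore contains a fall that has nothing to do with the programme.

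A comparator normally absorbs such a fall, but only if it was selected in the same way. A whole district matched to a whole district has no selected 2018 peak, so subtracting its change leaves the artefact in place. At stake is the primary aim: whether a fall of 4.7 points or more would mean anything about the programme.

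**Working it through.** **1. The plan's own figure.** The 4.7-point critical difference comes from a cited report, and the article does not give its inputs. A plain two-sample binomial limit, z·√(2p(1−p)/n), with p = 0.264 (Belconnen 2018, Introduction) and z = 1.96, gives 8.6, 7.7 and 7.1 points at n = 200, 250 and 299. So 4.7 cannot be reproduced this way. That does not show it to be wrong, and it is used below as stated.

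**2. Suburb size (assumption: equal split).** 200/9 = 22 and 299/9 = 33 children per suburb per census; 28 is taken as a middle value.

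**3. Closed form, no true trend, selection on the primary index alone.**
- Standard error of one suburb's proportion: SE = √(0.264 × 0.736 / m) = 9.4, 8.3 and 7.7 points at m = 22, 28 and 33.
- Expected chance excess in 2018, given that 2018 exceeds 2012: SE/√π = 5.3, 4.7 and 4.3 points. At m = 28 this is 8.33/1.772 = 4.7.

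**4. Simulation of the full rule, no intervention effect.** Assumptions: 25 candidate suburbs of equal size; five domains with latent correlation 0.5; 26.4% vulnerable on one or more; worsening read as 2018 above 2012 on the summary index and on at least three domains; up to nine eligible suburbs pooled.

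| True trend | Children per suburb | Expected fall 2018 to 2024 (points) | Share of runs with fall ≥ 4.7 |
|---|---|---|---|
| None | 22 / 28 / 33 | 7.5 / 6.2 / 5.9 | 0.70 / 0.63 / 0.63 |
| Suburb slopes to 2018, then level; latent SD 0.1 per wave | 28 | 5.0 | 0.54 |
| Same, taking the highest 2018 levels among eligible suburbs | 28 | 5.3 | 0.58 |
| Same slopes plus a common worsening | 28 | 3.9 | 0.44 |
| Slopes to 2018, then level; SD 0.2 | 28 | 3.1 | 0.35 |
| Slopes continuing to 2024; SD 0.1 | 28 | 0.2 | 0.20 |
| Continuing slopes plus a common worsening | 28 | rise of 3.5 | 0.06 |
| Slopes to 2018, then level; SD 0.1 | 60 / 100 / 150 | 2.7 / 1.7 / 1.2 | 0.225 / 0.095 / 0.005 |

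With latent correlation 0.6 and about 27% vulnerable, the no-trend falls are 7.3, 6.2 and 5.5 points. With no trend and larger suburbs they are 4.1 at 60 children and 3.5 at 75.

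**5. Baseline outside the selection window (2021 to 2024).** In the scenarios at 22-33 children with no trend, or with slopes that level off after 2018, the mean fall lies between −0.3 and +0.2 points. The 4.7 mark is reached in 12-17% of runs.

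**6. Comparator, changes from 2018.** With no true trend, the difference in change against an unselected control still shows a fall of 7.7, 6.3 and 5.7 points at 22, 28 and 33 children. Against suburbs passing the same rule it is within 0.3 points of zero. When continuing slopes are added, the error with an unselected control runs from −7.7 to +8.0 points. With a same-rule control it stays within about 0.5.

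**7. Comparator, 2024 cross-section.** The selected suburbs lie 0.3 to 6.7 points above the average of all candidates in the scenarios of step 5, and up to 11.7 above with continuing slopes. Against an unselected district, this works against the intervention.

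**8. Averaging 2012, 2015 and 2018 as baseline.** The bias is near zero without a trend. With continuing slopes (SD 0.1) the average produces a spurious worsening of about 7 to 8 points, and 10.9 with a common worsening.

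**The case against.** **The formal hypothesis uses 2021.** The second hypothesis and two statements of the time comparison set 2021 against 2024, and from 2021 the artefact essentially vanishes. This stands, and it makes the point conditional. It does not dispose of it: the section that defines the outcome gives 2018 as baseline and states reasons for excluding 2021, so a reader cannot tell which comparison will be made.

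**The bias is not always towards benefit.** A reader might infer that the whole evaluation is tilted in the programme's favour. The documents do not support that. The first hypothesis is a 2024 cross-section, where an unselected district biases against the intervention or hardly at all.

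**No true trend is the extreme case.** The Introduction reports rising vulnerability across the ACT over 2012-2018. If real suburb trends continue, the fall from 2018 is absent or reversed. This stands.

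**Suburbs may be larger.** Sample size estimates can be read as 500-600 at-risk children making up about 40% of a sample, hence 500/0.4 = 1,250 to 600/0.4 = 1,500 children, or 139 to 167 per suburb over nine. At 150 the artefact was only 1.2 points in the scenario run. However, Quantitative analysis explicitly expects 200-299 children, and Table 1 gives the threshold for that size only.

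**The match may be finer than it looks.** The Abstract claims matching on trends, and the first hypothesis speaks of control suburbs. The full protocol may say how these are chosen, and an article's silence on that is no fault. What can be said is that the article's one concrete matching claim concerns districts, while the intervention group is a selected subset of one.

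**The two selection rules are a separate matter.** They are. The discrepancy needs reconciling but is not evidence of regression to the mean.

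**Conclusion.** The concern holds conditionally. If 2018 is kept as baseline, regression to the mean alone can reach or exceed 4.7 points. The expected fall is about 5.5 to 7.5 points with no true trend and 22-33 children per suburb. It rests on that equal split, on the assumed number of candidate suburbs and domain correlation, and on reading worsening as 2018 above 2012.

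A reader might go further and conclude that the artefact will exceed the threshold. The documents do not support that: with real trends or larger suburbs the expected fall can lie below 4.7, vanish or turn into a rise. Nor is 2018 the only stated baseline.

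Two parts do not depend on the simulation assumptions. The sections contradict each other on the baseline. And a control not selected by the same rule leaves the change from 2018 open to error, in a direction that depends on unknown trends.

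**What to change.** 1. Define the comparator as the Tuggeranong suburbs that meet the same 2012-2018 worsening rule, matched to the nine on level and trend and fixed before 2024 data are seen.
2. Base the effectiveness conclusion on the difference in change between areas, not on the within-area change alone.
3. Settle one baseline across Developmental vulnerability, Sample size estimates and Quantitative analysis. If it is 2018, do not read the uncontrolled before-after change against 4.7 points as an effect.
4. Use the 2012/2015/2018 average only as a sensitivity analysis, because continuing trends make it misleading as the primary baseline.
5. Reconcile Sample size estimates with Participants and Design and intervention on the selection rule and the number of districts, and name regression to the mean among the limitations.

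The cost is a reselection from existing suburb-level census data plus wording. The price is fewer control children than the whole district would supply, and a wider margin, since a difference of two changes is less precise than a single change.
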